### Trial data collection

All required study data will be captured in a set of purpose-built eCRFs. Access to the eCRFs will be restricted, via a trial-specific web portal, and only authorised personnel will be able to enter data. The site principal investigator or their designee(s) will be responsible for all entries into the eCRF and will confirm that the data are accurate, complete and verifiable. Data will be stored in a Microsoft SQL Server database at the University of Glasgow Clinical Trials Unit, which has an ISO 9001 quality management system and ISO 27001 for information security.

Participants will be able to complete their questionnaires on a paper CRF (that will then be entered into the eCRF by the local research team) or to complete them electronically. Where completed electronically, data will be entered directly into a participant-facing version of the eCRF. As the eCRF will be adapted for self-completion, consent will be sought to use the participant contact details provided for recontact to verify responses as needed. Participants who consent to long-term follow-up of their outcomes using routine data, NHS/Community Health Index numbers will be collected to facilitate the potential collection of data in the future.

Regular data management/cleaning will be undertaken to assess data quality. Quality assurance checks will be performed to monitor the level of missing data and the timeliness of data entry and check for inconsistent data.

### Process evaluation

The process evaluation will assess the following research questions:

Was the intervention delivered as intended?What adaptations were made/required in the intervention and do these impact outcomes?Was the intervention used as intended?What mechanisms explain any observed impact on patients’ HRQoL and other patient and caregiver outcomes?What are the perspectives of patients, caregivers and service providers on the experience of being involved in REACH-HF?What factors are associated with variation in intervention effectiveness among intervention recipients?What adaptations were made within the service and did these impact fidelity and outcomes?

The process evaluation will use mixed methods at multiple case levels (patient, facilitator and centre) to test the programme theory in the population with HFpEF, identifying which components and configurations are best suited to meet their needs.^31 32^ The process evaluation will identify refinements of the programme theory, to optimise implementation and ensure that the essential ingredients of future interventions are better identified, interrogated and tested.^33^ As the analysis progresses, the implementation strategy will be revisited, focusing on potential outcomes such as Non-adoption, Abandonment, Scale-up, Spread, Sustainability Framework.^34^ This will maximise the clinical application of our research findings and enhance the capacity of staff working with participants with HFpEF to implement the intervention.

The participants in this process evaluation will comprise a subsample of patients, caregivers and REACH-HF facilitators taking part in the REACH-HFpEF trial. To answer the research questions, this mixed-method process evaluation will use trial primary and secondary outcomes and collect additional qualitative data (eg, intervention session recordings and interviews). The process evaluation will use multimodal longitudinal data.^35 36^

#### Process evaluation 1: participant and caregiver experience

15–20 patients (and 10 caregivers of these same patients) will be purposively selected and invited to take part in semistructured interviews. Patients will be chosen to represent, for example, diversity in terms of site/facilitator, sex, ethnicity, presence of a caregiver and baseline MLwHF Questionnaire total score.

The research team will interview each of these patients/caregivers at 4 months after the baseline visit (ie, immediately after intervention delivery is complete) and 12 months after the baseline visit. This will allow capture of patient and caregiver narratives over time, in relation to both intervention receipt and the longer-term impact/maintenance of self-care following the intervention. We will audio or video record these interviews, which may be conducted in person (if possible) or remotely (if not). Recording will use encrypted recording methods (either via password-protected online meeting software or an encrypted voice recorder). Written consent will be obtained prior to face-to-face interviews.

Topic guides for the interviews have been codeveloped with the patient and public involvement (PPI) advisory group. Interviews are designed to last between 30 min and 60 min. The researcher will endeavour to interview the patients without the caregiver present, where possible, and be mindful of the patient’s symptoms, such as fatigue or breathlessness, which may make an interview burdensome for the participant. The two interviews (and potentially selected segments of the intervention session recordings which represent good practice) will be transcribed verbatim. Thus, for each patient, their qualitative dataset is likely to comprise: two face-to-face meetings with their facilitator, five telephone meetings with their facilitator and two interviews with the process evaluation team.

#### Process evaluation 2: REACH-HF facilitator’s experience

In addition, 15 REACH-HF facilitators will be invited to take part in the process evaluation.

The process evaluation team will send an email to the participating facilitators with a brief questionnaire about their clinical background. This short questionnaire will either be completed in an electronic Word document and returned via email, or by following a link in the email to an electronic questionnaire (eg, using the electronic questionnaire platform Qualtrics). The process evaluation team will endeavour to sample REACH-HF facilitators to represent diversity in, for example, site, background training (eg, physiotherapy and nursing) and years of experience in delivery of cardiac rehabilitation (gathered using the clinical background questionnaire, see above). A topic guide will inform the interview, premised on the existing literature and gaps in current knowledge about intervention delivery. These interviews will be conducted either in person or remotely via telephone/web-call.

Verbatim interview transcripts will be organised and coded using MAXQDA. A framework analysis will be conducted, and sections of data relating to the aims of this research will be assigned a code that summarises the content either descriptively or interpretively. Codes with common features will be grouped together in themes, before finally being assigned to overarching themes. Where possible, data about self-reported behaviour from the interviews will be compared with observed behaviour evident in the intervention session recordings. A second qualitative researcher from the team will conduct independent analysis of a subset of the data. The researchers’ reflexive memo notes will enhance the integrity of the analysis.

The analysis will characterise patients’ and caregivers observed and self-reported responses to the intervention and link these responses to engagement with the intervention and perceived benefit, identifying interpersonal processes that shape the effectiveness or ineffectiveness of the intervention. At 4 months, patients’ and caregivers’ engagement with, response to and use of the REACH-HF manual will be characterised and differences between patients noted. At 12 months, overall use and benefit and maintenance of self-care behaviours and coping skills will be characterised and linked to individual differences in 4-month responses. Analysis will explore both patients’ and caregivers’ experiences of participation in the intervention and explicitly examine any potential impact of caregiver presence on patient adherence to the REACH-HF intervention.

#### Process evaluation 3: fidelity of intervention delivery

Facilitator-patient interactions (face-to-face and phone) for up to 60 patients will be audio-recorded (approximately 5–6 interactions taking 4–5 hours per patient). Recordings will be assessed using a previously developed and tested fidelity assessment checklist.^8^ The 12-item checklist uses a 0–5 rating scale based on the Dreyfus scale for assessing clinical competence.^37^ It focuses on assessing the quality of delivery of key delivery processes, such as the use of a patient-centred communication style, making a plan of action and encouraging self-monitoring of progress (particularly with the exercise programme). Intervention delivery fidelity data will be presented descriptively (mean scores with SD or 95% CIs) and broken down by site and by facilitator (as well as the calculation of overall delivery fidelity scores) for each checklist item. This will clarify how well intervention components were delivered and may identify ways to optimise delivery for future implementation. It will also allow researchers to describe variability in fidelity of delivery across patients and facilitators.

In addition, segments of the recordings that represent clear examples of good practice associated with each component of delivery (each item on the checklist) will be identified by noting the start/end timestamps of the segment within the audio file. These segments will be transcribed and collated for informing future REACH-HF training. Any information that might be used to identify the patient or the facilitator within the transcript will be redacted.

We will report descriptive statistics to summarise the fidelity of intervention delivery for each checklist item and will (descriptively and anonymously) examine variations between sites. Synthesis of the analysis of the intervention delivery fidelity and the interview data will enable a qualitative evaluation of potential pathways and barriers to improvement, which will pay attention to discrepancies between expected and observed outcomes, to understand how context influences outcomes and to provide insights to aid future implementation.

#### Process evaluation 4: facilitator checklist and log

REACH-HF facilitators will be asked to complete a brief self-rated fidelity checklist after each session they deliver. This comprises questions about the same 12 delivery fidelity components described above and allows the facilitators to rate the occurrences of each feature (absence, minimal, some, sufficient, good, very good and excellent). An independent observer rating is resource-intensive, while self-rated assessment may provide a pragmatic, real-world alternative to monitor delivery quality. The validity of the self-rating method will be checked by examining the correlation with observer-rated intervention delivery fidelity. We will also explore in the qualitative interviews whether use of the checklist facilitates/encourages reflexive practice and, in doing so, the quality of implementation.

Additionally, facilitators will be asked to complete a facilitator contact log for each participant. This log is a one-page pro forma designed to capture time, expenditure and any other resources required for the implementation of REACH-HF, as well as any adaptations made to the intervention for individual patients. It will capture data for both assessment of the fidelity of REACH-HF delivery and economic analyses.

A detailed process evaluation analysis plan will be drafted prior to study data lock and agreed with the Trial Management Group (TMG) and TSC.

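### Correlation with observer scores, the only check named for facilitator self-rating, cannot show whether self-ratings run systematically high

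*Protocol article*

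**What the plan says.** Two sections of the protocol article describe two ratings of the same behaviour.

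- **Observer rating** (Process evaluation 3: fidelity of intervention delivery). The material is a sample of recordings: "Facilitator-patient interactions (face-to-face and phone) for up to 60 patients will be audio-recorded", at roughly five to six interactions per patient. On the instrument: "The 12-item checklist uses a 0–5 rating scale based on the Dreyfus scale for assessing clinical competence". Results are to be given as mean scores with SDs or confidence intervals, by item, site and facilitator.
- **Self-rating** (Process evaluation 4: facilitator checklist and log). Facilitators complete a short checklist after every session. On content: "This comprises questions about the same 12 delivery fidelity components described above". The response options are seven labels: "absence, minimal, some, sufficient, good, very good and excellent".

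Process evaluation 4 gives the reason for collecting both. Observer rating takes a lot of resource, whereas "self-rated assessment may provide a pragmatic, real-world alternative to monitor delivery quality". The one quantitative check of that idea is: "The validity of the self-rating method will be checked by examining the correlation with observer-rated intervention delivery fidelity". The section names no measure of agreement or of mean difference and no mapping between the seven labels and the 0 to 5 scale. It closes by saying that a detailed process evaluation analysis plan will be drafted before data lock.

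**The concern.** If self-rating is to stand in for an observer when delivery quality is monitored, the level of the score matters as well as its ordering. The article itself summarises observer-rated fidelity as mean scores, and a substitute would naturally be read the same way. A facilitator group that follows the observer's ordering but marks itself a grade too high would produce means that overstate quality, and the planned check would not show it.

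The differing scales make this harder to see. A correlation can be computed between a 0 to 5 score and a seven-label score without deciding which label corresponds to which number. The question of level then never has to be faced.

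What is at stake is the conclusion the process evaluation draws about the self-rating checklist. A high correlation could be reported as support for its validity while leaving open whether its scores mean the same as the observer's.

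**Working it through.** **Inputs from the article.** Observer scale 0 to 5, so 6 levels. Self-rating scale: 7 labels. Both cover the same 12 components. Recorded interactions: at most 60 × 5 = 300 to 60 × 6 = 360. The article gives no figure for this check that could be reproduced.

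**Step 1: what a constant shift does.** Let O be the observer score, S the self-score without bias, and d a constant over-rating.

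- Pearson correlation: r(O, S + d) = cov(O, S) / [SD(O) × SD(S)]. The shift d drops out.
- Spearman correlation: adding d leaves the ranks unchanged, so it drops out here too.
- Mean difference, self minus observer: it rises by exactly d.
- Lin's concordance: 2 cov(O, S) / [var(O) + var(S) + (difference in means)²]. It falls as d grows.

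This step needs no assumption about the data.

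**Step 2: size, with assumed values.** The article gives no SDs for fidelity scores, so these are assumptions: both raters on a common 0 to 5 scale, true-score SD 0.5, independent rating error SD 0.25 for each rater, no mean bias before the shift. Then:

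- cov(O, S) = 0.5² = 0.25
- var(O) = var(S) = 0.25 + 0.0625 = 0.3125
- r = 0.25 / 0.3125 = 0.80 for every d
- concordance = 0.50 / (0.625 + d²)

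| Over-rating d | Pearson r | Concordance | Mean difference |
|---|---|---|---|
| 0 | 0.80 | 0.50 / 0.625 = 0.80 | 0 |
| 0.5 | 0.80 | 0.50 / 0.875 = 0.57 | 0.5 |
| 1.0 | 0.80 | 0.50 / 1.625 = 0.31 | 1.0 |
| 1.5 | 0.80 | 0.50 / 2.875 = 0.17 | 1.5 |

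A simulation of 300 sessions (true mean 2.5) gave the same values to two decimals, with Spearman's coefficient steady at about 0.78.

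**Step 3: a bounded scale.** Real item scores are whole numbers with a ceiling, which could make over-rating visible in r. A second simulation used integer scores limited to 0 to 5, true mean 2.5 and SD 1, error SD 0.5, again with 300 ratings.

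| Intended over-rating | Pearson r | Concordance | Mean difference |
|---|---|---|---|
| 0 | 0.75 | 0.74 | 0.00 |
| 1 | 0.74 | 0.54 | 0.96 |
| 2 | 0.68 | 0.26 | 1.78 |

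The ceiling lowers r slightly. A reader who saw 0.74 or 0.68 could not tell over-rating from ordinary rating error.

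**Step 4: how far agreement depends on the mapping.** Number the labels k = 0 (absence) to 6 (excellent). Three simple mappings to 0 to 5 are: merge the two lowest labels, max(k − 1, 0); merge the two highest, min(k, 5); or rescale linearly, 5k/6. The label good (k = 4) becomes 3, 4 or 3.33. For k = 1 to 5 the two merging rules differ by a full point; for k = 0 and k = 6 they do not differ. So the measured bias is partly a product of the mapping. It should therefore be fixed in advance and tested against an alternative.

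**The case against.** The best case for the article has four parts.

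1. **Detail is deferred.** A process evaluation analysis plan is still to come, and naming correlation does not exclude agreement statistics. It is fair that a mapping, a kappa or an interval method need not appear in an article. But the article goes beyond silence: it names a method for a stated purpose, and that method does not fully serve the purpose. A plan that simply carried the sentence forward would inherit the gap.
2. **Correlation is a sensible first step between differently anchored instruments.** This stands. Association is real evidence about validity, level bias is only one threat to it, and correlation would suffice if self-ratings were used only to rank sessions or facilitators. The unreproduced checklists may also contain anchors that link the two scales.
3. **A uniform shift can be recalibrated.** True, but only once it has been estimated, and correlation does not estimate it.
4. **Self-report is compared with behaviour elsewhere.** Process evaluation 2 says, where possible, "data about self-reported behaviour from the interviews will be compared with observed behaviour evident in the intervention session recordings". That comparison uses interview accounts and is qualitative. It does not compare checklist scores.

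Some stronger readings are tempting and the document does not support them. A reader might infer that sessions will be pooled into one correlation that ignores facilitators and patients; the article states no coefficient, unit or model. A reader might infer that a biased tool will be carried into NHS monitoring; the article says only that self-rating may be an alternative, sets no pass mark and commits to no adoption. A reader might picture a correlation of 1.00 with every session graded too high; that needs identical over-rating, no rating error and no ceiling.

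**Conclusion.** The point holds as a minor one. The named check can show that self-ratings track observer ratings; it cannot show whether they run high, and the proposed use makes that question relevant. That part is algebra and rests on no assumption. The sizes (concordance falling from 0.80 to 0.31 at one point of over-rating while r stays at 0.80) rest on assumed SDs and a common scale, and are illustrations only. Nothing in the article indicates that facilitators will in fact over-rate themselves.

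The consequence is confined to what is concluded about the self-rating checklist. The fidelity results in Process evaluation 3 come from the observers. The primary outcome, the secondary outcomes and the economic evaluation do not use this check.

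**What to change.** In the process evaluation analysis plan, before data lock:

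- keep the correlation, described as evidence of association;
- pre-specify a mapping of the seven labels to 0 to 5, chosen from the wording of the anchors before paired scores are examined, with one alternative mapping as a sensitivity check;
- on the recorded sessions, report the mean self-minus-observer difference with limits of agreement, and a weighted kappa (items) or absolute-agreement ICC (total score);
- give intervals that allow for repeated sessions per facilitator and per patient.

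The cost is a few lines of text and a modest extra analysis of data already being collected. The downside is small: agreement results depend partly on the mapping, which the alternative mapping makes visible.

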### Economic evaluation

Economic analysis will be performed to establish the cost-effectiveness of REACH-HF plus usual care compared with usual care alone. Following on from the results of the economic evaluation pilot study,^13^ a within-trial cost-utility analysis will be conducted. Pilot study findings revealed differential resource distributions across primary, secondary and social care as well as impacts on informal carer time and costs. Bespoke data capture instruments have been developed to ensure capture of all relevant resource use from both an NHS/Personal Social Services (PSS) perspective, as well as a broader societal perspective. There is evidence of insensitivity of the EQ-5D-5L in patients with mild HF.^3638^,^41^ A recent study comparing the EQ-5D-5L and short-form six-dimension (SF-6D) in elderly participants with HF recommends use of SF-6D in those with milder disease and economic outcomes.^39^ Therefore, we propose to use both the SF-6D (from SF-12) and the EQ-5D-5L. As recommended by NICE economic evaluation guidance, the base-case perspectives will be that of the UK NHS and PSS.^42^ Further, a broader societal perspective, accounting for resource use, productivity (employment) and personal cost impacts faced by patients and their carers will be considered in sensitivity analyses, along with a scenario analysis incorporating HRQoL values obtained from mapping MLwHF Questionnaire scores to EQ-5D utilities, using a validated mapping algorithm.^43 44^ The base case economic evaluation will estimate the incremental cost per QALY associated with the REACH-HF intervention, compared with usual care alone, and will be reported in line with updated reporting guidelines for economic evaluations.^45^ The wider societal perspective will incorporate resource use, productivity (employment) and personal costs. Missing resource use and outcome data will be handled using multiple imputation.^46^ If within-trial results reveal between-group differences in HRQoL, a decision analytic model will be developed to estimate the cost-effectiveness results over a lifetime horizon.

A detailed health economic analysis plan will be drafted prior to study data lock and agreed with the TMG and TSC.

### Statistical analysis

Participation from screening to completion of the final follow-up assessment will be reported. Baseline patient characteristics and outcome scores will be summarised descriptively.

The primary statistical analysis for both primary and secondary outcomes will take an intention to treat approach (according to randomised allocation) based on complete data. For continuous outcome measures, mixed-effects regression will be used with a random effect of recruiting site and adjusting for baseline outcome score and minimisation variables. Additional clustering of outcomes due to therapist effects will be accounted for in sensitivity analyses.

A number of secondary analyses will be undertaken. Patterns and reasons for missing outcome data will be assessed, and sensitivity analyses will use appropriate imputation models to assess the impact of missing data. Potential subgroup treatment effects will be explored by adding treatment-by-subgroup interaction terms to analysis models. Potential subgroups assessed will include sex, study site and participant baseline NT-proBNP levels, ejection fraction and important markers of inequity, such as age, socioeconomic status and having a carer. Since the trial is powered to detect overall differences between the groups rather than interactions of this kind, these subgroup analyses will be regarded as exploratory. Before the start of recruitment, the TMG (with TSC approval) will be asked to define the minimum adherence to the REACH-HF intervention required to indicate compliance. Complier average causal effects analyses will be used to estimate the causal intervention effect in relation to each outcome.

Adherence will be defined using criteria adapted for the delivery processes proposed for the current study. These criteria will be developed with the TMG, building on the criteria used in the prior multicentre REACH-HF trial in people with HFrEF.^11^ Associations between physiological, cognitive and demographic factors and intervention adherence will be explored.

Estimated between-group differences will be presented using both absolute and relative measures, with associated 95% CIs, where appropriate. No correction of p values for multiplicity of testing will be undertaken. However, the analysis for the primary outcome will be performed before all other analyses, and the p values of all subsequent analyses will be interpreted in the context of multiple testing. No interim analyses are planned. Safety/adverse event outcomes will be reported descriptively by group.

A detailed statistical analysis plan will be drafted prior to study data lock and agreed with the TMG and TSC.

